### B1. PURPOSE OF PROTOCOL

The purpose of this study is to investigate the effects of a) a homeopathic supplement marketed for heartburn symptoms (Acidil) and b) components of the placebo response (the doctor-patient interaction and belief/expectation) on symptoms and health-related quality of life (HRQL) in patients with gastroesophageal reflux disease (GERD). This study is designed as a pilot trial to assess safety and feasibility and to provide preliminary estimates of effect sizes in anticipation of conducting a larger trial in the future.

**Aim 1:** To determine the safety and feasibility of conducting this 2x2 factorial design randomized controlled trial in this patient population.

**Hypothesis 1:** This study design will be both safe and feasible and subject recruitment will not be difficult (i.e., no significant adverse events and greater than 90% of those who enroll will complete the study protocol).

**Aim 2:** To determine whether changes in GERD-specific, dyspeptic, and overall symptoms and HRQL are significantly different between subjects receiving Acidil and subjects receiving an identical placebo.

**Hypothesis 2a:** Compared to subjects receiving placebo, more subjects receiving Acidil will experience a 50% or greater improvement in GERD symptom severity during the last 7 days of the study compared to baseline.

**Hypothesis 2b:** The dynamic trajectory of symptom changes over time will differ between the Acidil and placebo groups as expected according to homeopathic theory.

**Hypothesis 2c:** Subjects receiving Acidil will report greater improvement in disease-specific and overall quality of life compared to the placebo group.

**Aim 3:** To determine whether changes in GERD-specific, dyspeptic, and overall symptoms and HRQL are significantly different between subjects receiving an expanded clinical interview similar to a homeopathic consultation (enhanced physician-patient interaction) vs. a standard allopathic interview, and to determine whether any treatment responses are mediated by preconceived beliefs and expectations regarding treatment efficacy.

**Hypothesis 3a:** Compared to subjects receiving the standard clinical interview, more subjects receiving an expanded clinical interview will have a 50% or greater improvement in GERD symptom severity during the last 7 days of the study compared to baseline.

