## **B. Statistical Considerations**

### **Sample Size Justification:**

We will screen a sufficient number of subjects to consent/enroll 24 subjects total into the study, 6 subjects in each of the 4 groups. This number was determined to ensure that we can complete enrollment within a 6-12 month time frame to assess study feasibility as our primary outcome.

As this is a pilot feasibility study, we do not anticipate having adequate power to show significant differences in treatment effects between groups, but do hope to generate estimates of effect sizes and demonstrate trends. Our chief secondary outcome will be the percent of subjects with 50% or greater improvement in heartburn symptom severity for the last 7 days of the study compared to baseline (compare groups 1+3 vs. groups 2+4 [Aim 2a] and groups 1+2 vs. groups 3+4 [Aim 3a]). We will also assess the percent of subjects with dynamic changes in heartburn symptom severity during the study period compared to baseline (compare groups 1+3 vs. groups 2+4 [Aim 2b]).

Table 2 illustrates power estimates using the Fisher exact test for between group differences ranging from 0.25 – 0.4 for an alpha of 0.05 and sample sizes of 24 subjects and 20 subjects per group (combining groups 1+3 and 2+4 or groups 1+2 and 3+4 for all analyses). We anticipate that we will have 30-50% power to detect a difference between groups. These power calculations are based on the assumption of no interaction effect.

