### Data Analysis:

All study data will be transcribed from paper surveys and entered into a REDCap database for data management. We will perform random screening of entered data to ensure accuracy. At the time that the REDCap database is translated into a SAS database for data analysis, the 2 main intervention codes (i.e., Acidil vs. placebo and standard vs. expanded interview) will be recoded by a member of the study team who did not have any subject contact ([name]) so that the principle data analyzer ([name]) is blinded to all study group assignments during the data analysis process. Initial analysis will include descriptive statistics assessing the baseline demographics, GERD and dyspepsia symptom frequency and severity, and HRQL among subjects in each of the 4 groups. All analyses described below will be intent-to-treat analyses and include an interaction term to account for possible interaction of the 2 main interventions in this study. The SAS database will not include any PHI and will be stored on the study investigator's H drive and thus will be password protected and behind a secure firewall.

**Hypothesis 1:** This study design will be both safe and feasible and subject recruitment will not be difficult.

Study safety will be established if there are no major adverse events attributed to Acidil and no statistically significant increase in minor adverse events between the Acidil and placebo groups. Feasibility will be established if we can demonstrate recruitment and retention of >90% of subjects within the pre-specified 6-12 month time frame.

**Hypothesis 2a:** Compared to subjects receiving placebo, more subjects receiving Acidil will experience a 50% or greater improvement in GERD symptom severity during the last 7 days of the study compared to baseline.

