##### **Exclusion criteria:**

- \*1. Subjects who have taken a proton pump inhibitor (PPI) or H2 receptor blocker within 2 weeks of the initial study visit.
2. Subjects with Crohns disease, systemic sclerosis, known active ulcer disease, gastric cancer, Barrett's esophagitis, significant pain or difficulty with swallowing, heavy alcohol use (defined by > 6 drinks/week for women and > 13 drinks/week for men), concurrent pregnancy (beyond first trimester as the physiology of heartburn symptoms in pregnant women is different from that in the non-pregnant population), dementia, or uncontrolled psychiatric disease.
3. Subjects unable to complete a paper symptom diary for 6 of 7 days prior to their baseline visit.
4. Subjects whose symptoms are predominantly dyspeptic more than heartburn or reflux.
5. Subjects who have used homeopathy for GI symptoms or have received constitutional homeopathic treatment within the past 2 weeks.
6. Subjects taking herbal products or other supplements for GERD or dyspepsia related symptoms (includes peppermint oil).
7. Subjects who have taken > 12 doses of NSAIDS within the prior 30 days (aspirin  $\leq$  325 mg daily is allowed).
8. Subjects with lactose intolerance. Our rationale: the Acidil and placebo tablets both contain lactose. Lactose intolerance is associated with GI symptoms, some of which overlap with symptoms that we are measuring in this study. Excluding lactose intolerant individuals will help make our data more interpretable.

\*If this population of subjects is too difficult to recruit, we will instead:

A) offer to enroll subjects if they wish to taper off their current medications. This will only be done if they do not have known Barrett's esophagus and are on a low dose PPI or H2 blocker. Subjects will be given standardized instructions for how to taper off of these medications using oral antacids as a bridge.

If we are unable to reach recruitment targets using secondary strategy A, we will also:

B) try to recruit subjects currently on stable drug therapy (no changes in PPI or H2 blocker dose x 2 weeks) with refractory GERD symptoms 3 or more days per week.

If we enroll subjects in groups A and/or B, we will modify our randomization approach to stratify by the different groups of subjects (i.e., based on status of PPI/H2 blocker use: none, recent, current) enrolled in the study so that they are equally distributed between arms.

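### The primary feasibility rule is blind to which population supplied the recruits, so it can be met after the originally intended population has proved too hard to enrol

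*Protocol*

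**What the plan says.** Aim 1 in section B1 is "To determine the safety and feasibility of conducting this 2x2 factorial design randomized controlled trial in this patient population". Section B3.B, Sample Size Justification, makes feasibility the primary outcome and fixes the size by enrolment time: "We will screen a sufficient number of subjects to consent/enroll 24 subjects total into the study, 6 subjects in each of the 4 groups", and "This number was determined to ensure that we can complete enrollment within a 6-12 month time frame to assess study feasibility as our primary outcome".

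Under Data Analysis, Hypothesis 1 reads "This study design will be both safe and feasible and subject recruitment will not be difficult", and its success rule is "Feasibility will be established if we can demonstrate recruitment and retention of >90% of subjects within the pre-specified 6-12 month time frame".

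Section B3.C, Exclusion criteria, stars the criterion that bars anyone who took a PPI or H2 blocker in the 2 weeks before the first visit. The note to the star begins "If this population of subjects is too difficult to recruit, we will instead". It then allows (A) subjects who wish to taper off a low-dose PPI or H2 blocker and, if targets are still missed, (B) subjects on stable therapy whose symptoms persist. If either is used, "we will modify our randomization approach to stratify by the different groups of subjects", with PPI/H2 use graded none, recent or current.

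**The concern.** The note to the exclusion criteria and the feasibility rule deal with the same event and do not refer to each other. The note's trigger is that the intended subjects are too hard to recruit. Hypothesis 1 says that recruitment will not be hard. Once the trigger is met, the hypothesis has failed for that population. Yet fallback subjects are enrolled and randomised in the same trial, the rule speaks of subjects without qualification, and nothing removes the fallback subjects from the count.

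The pilot is run to prepare a larger trial. A pooled statement that recruitment was feasible could lead the sponsor to plan that trial with the starred criterion in place, at an accrual rate which the untreated population did not deliver.

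**Working it through.** **1. The target.** 4 groups × 6 subjects = 24, which agrees with the stated total. The size was set by enrolment time, so no power formula enters.

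**2. The threshold.** 90% of 24 is 0.90 × 24 = 21.6, so more than 90% means at least 22. Check: 22/24 = 91.7% passes and 21/24 = 87.5% does not.

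**3. What the rule asks of the original population.** Let k be the number of the 24 who meet the starred criterion and 24 − k the number who enter through A or B. The rule depends on the total enrolled, the number retained and the time taken. It does not depend on k, so any k from 0 to 24 is compatible with a pass. The minimum is 0 of 24.

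**4. What a pooled verdict can hide (illustration; the split is assumed).** Suppose 24 subjects are enrolled by month 12, with k = 8 from the original population.

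- Pooled rate: 24/12 = 2.0 per month.
- Rate in the original population, if it was open throughout: 8/12 = 0.67 per month.
- Ratio: 2.0/0.67 = 3.

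The rule is met on recruitment, but a later trial limited to untreated subjects would recruit at one third of the reported rate.

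**5. The passages side by side.**

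| Place | Content | Effect of opening A or B |
|---|---|---|
| B3.B, Hypothesis 1 | recruitment is not hard | none stated |
| B3.B, success rule | over 90% of subjects, 6–12 months | none stated |
| B3.C, starred note | fallbacks if the population is too hard to recruit | randomisation stratified |

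No section says that opening A or B fails the recruitment criterion, and no number or date defines when the trigger is met.

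**6. The time limit.** 24/6 = 4.0 per month at the short end and 24/12 = 2.0 at the long end. With Poisson accrual at an assumed 3 per month, the chance of 24 enrolled is about 0.10 by month 6 and 0.99 by month 12. The natural reading takes 12 months as the limit, and naming it removes any doubt.

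**7. Cost of using the stratum.** An ANOVA with two factors and their interaction fits 4 cell means and leaves 24 − 4 = 20 residual degrees of freedom. A three-level PPI/H2 factor takes 2 and leaves 18. Crossing 4 groups with 3 strata gives 24/12 = 2 subjects per cell on average, too few to support extra terms in a logistic model that already carries an interaction.

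**The case against.** The best defence is that section B1 describes the trial's patients as having GERD, not as being off acid suppression. Fallback B keeps the requirement of symptoms on 3 or more days a week. A pilot that fills its places through a fallback written down in advance has then shown feasibility in GERD patients. Medication use is recorded at both visits and PPI/H2 status would become a randomisation stratum, so the mix of subjects would be known. The rule also does not say in words that fallback subjects count. That follows from its unqualified reference to subjects.

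Part of this stands. Nothing is concealed, and the issue arises only if a fallback is opened. But the broad reading does not reconcile the starred note with Hypothesis 1: the note uses difficulty of recruitment as its trigger, and the hypothesis denies that difficulty. Even on that reading, a pooled verdict does not say which eligibility criteria a larger trial could use.

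A reader might infer more than the protocol supports:

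- *That the 6–12 month range makes a month-11 finish both a pass and a failure.* Month 11 lies inside the range and passes on the ordinary reading.
- *That B1 contradicts the Data Analysis section.* B1 expects "greater than 90% of those who enroll will complete the study protocol". The later rule uses the same 90% and adds recruitment, which Hypothesis 1 in B1 also mentions.
- *That the uncertainty of the retention criterion is a defect.* At true retention of 90%, 85% and 80%, the chance of at least 22 of 24 is 0.56, 0.28 and 0.11. Such figures describe any pilot of 24.
- *That leaving PPI/H2 status out of the models is an error.* An analysis plan not shown here may add it, and adjusting the logistic model for it is not clearly better at this size.

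**Conclusion.** The point holds in a limited form. The primary feasibility rule does not distinguish the original population from the fallback populations. It can be satisfied after the original population has been found too hard to recruit, with as few as 0 of 24 subjects from it. Followed as written, the plan could then report a wrong primary conclusion about recruitment in that population.

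This rests on two readings: that the unqualified word subjects covers everyone enrolled, and that the recruitment hypothesis concerns the population defined by the starred criterion. It has no effect if neither fallback is opened. How far a pooled verdict would mislead depends on the eventual split, which the protocol cannot give; the threefold figure belongs to the assumed split only. The rule is stated in the protocol itself and clashes with the protocol's own eligibility section, so this is not a detail left for later.

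**What to change.** **Feasibility rule (B3.B, Hypothesis 1, with a cross-reference from the starred note in B3.C).**

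- State that opening A or B means the recruitment part of Hypothesis 1 was not met for the original population.
- Report enrolment rate and retention separately for PPI/H2 status none, recent and current.
- Limit any feasibility conclusion to the population that supplied the subjects.
- Name 12 months as the outer limit.

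**Analysis, only if A or B opens and randomisation is stratified.**

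- Include PPI/H2 status in the planned ANOVA models for the continuous outcomes.
- Report the 50% responder outcome descriptively by stratum, and add no terms to the logistic model.

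**Cost.** Protocol wording, up to 2 of 20 residual degrees of freedom in the ANOVA models, and a recruitment criterion that is harder to claim as met. No extra subjects or data are needed, since medication use is already collected at both visits.

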### B3. DESCRIPTION OF RESEARCH PROTOCOL

#### A. Study Design – Overview, Methods, Procedures

##### Overview

We propose to conduct a single-center, pilot feasibility, 2x2 factorial design randomized controlled trial assessing the effect of a homeopathic supplement (Acidil) and components of the placebo response (doctor-patient interaction and beliefs/expectations) on symptoms and HRQL in patients with GERD over a 2 week time interval. The Acidil vs. placebo intervention will be double-blinded and the standard vs. expanded interview intervention (doctor-patient interaction) will be single-blinded. Randomization will be by permuted block randomization with block sizes of 4 and 8. We plan to enroll 6 patients into each group for a total of 24 subjects in the study according to the adjacent scheme. Subjects will be evaluated in the GCRC at BIDMC at two timepoints: baseline and at 2 week follow-up.

|                    | Acidil  | Placebo |
|--------------------|---------|---------|
| Standard Interview | Group 1 | Group 2 |
| Expanded Interview | Group 3 | Group 4 |

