A common measure for assessing treatment efficacy in GERD trials is assessment of the percent of subjects with a 50% or greater improvement in heartburn symptom severity (based on summation of symptom scores over time) using daily symptom diaries. We will perform this assessment by combining responses to the daytime heartburn, nighttime heartburn, and acid regurgitation questions on the daily symptom diaries for the last 7 days of the study compared to baseline. We will compare groups 1 and 3 with groups 2 and 4 using a logistic regression analysis and including an interaction term for the two study interventions. If there is no difference between groups, we will perform a secondary analysis using the GERD symptom severity score as a continuous variable to evaluate for potential trends.

**Hypothesis 2b:** The dynamic trajectory of symptom changes over time will differ between the Acidil and placebo groups. These differences may manifest as oscillations in symptoms in the Acidil group during the 2 week trial period, as well as changes in non-GERD and non-dyspeptic symptoms.

To assess for dynamic changes in treatment effects over time that may not be visible in end-point analyses such the one described in 2a above, we will perform a repeated measures analysis using generalized estimating equations and incorporating a time by treatment interaction term that will allow us to examine changes in GERD and dyspepsia symptom severity for the Acidil (groups 1+3) vs. placebo (group 2+4) group over the entire 2 week study period as well as look for differences in the number and frequency of non-GERD and non-dyspeptic symptoms based on data in the daily symptom diaries.

We will also assess the mean number of days without heartburn symptoms during the trial period for groups 1+3 and 2+4 as well as the mean number of days without dyspeptic symptoms during the

trial period (again groups 1+3 and 2+4) using the data from the GERD symptom diary.

**Hypothesis 2c:** Subjects receiving Acidil will report greater improvement in disease-specific and overall quality of life compared to the placebo group.

We will compare GERD-HRQL, Nepean Dyspepsia Index, and SF-12 scores between the Acidil and placebo groups (1+3 and 2+4), incorporating an interaction term for the two main treatment effects, using ANOVA.

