**Hypothesis 3a:** Compared to subjects receiving the standard clinical interview, more subjects receiving an expanded clinical interview will have a 50% or greater improvement in GERD symptom severity during the last 7 days of the study compared to baseline.

We will perform an analysis analogous to that for hypothesis 2a above by combining responses to the daytime heartburn, nighttime heartburn, and acid regurgitation questions for the last 7 days of the study compared to baseline on the daily symptom dairies comparing groups 1 + 2 with groups 3 + 4 using a logistic regression analysis and including an interaction term for the two study interventions.

**Hypothesis 3b:** Subjects receiving an expanded clinical interview will report greater improvement in disease-specific and overall quality of life compared to subjects receiving a standard clinical interview.

We will compare GERD-HRQL, Nepean Dyspepsia Index, and SF-12 scores between the standard (groups 1 + 2) and expanded (groups 3 + 4) interview groups, incorporating an interaction term for the two main treatment effects, using ANOVA.

**Hypothesis 3c:** Subject beliefs and expectations pre-treatment will partially explain changes in GERD and dyspeptic symptoms in the expanded vs. standard interview groups but not in the Acidil vs. placebo groups.

We will perform a logistic regression analysis including subjects' pre-treatment belief in CAM and scores on the credibility questionnaire using greater than 50% improvement in heartburn symptom frequency or severity during the last 7 days of the study compared to baseline (based on the daily symptom dairies) as the outcome. Due to the small sample size, we will be unable to adjust for potential confounders.

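### The chief responder analysis fits a saturated interaction model to four cells of 6; at Table 2's rates the averaged log odds ratio has no finite estimate in 23–51% of trials

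*Protocol*

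**What the plan says.** The Overview sets the size: "We plan to enroll 6 patients into each group for a total of 24 subjects in the study". Sample Size Justification repeats it as "consent/enroll 24 subjects total into the study, 6 subjects in each of the 4 groups". That section makes the 50% responder rate the chief secondary outcome, behind feasibility. It defines two pooled contrasts: groups 1+3 against 2+4 for Acidil, and groups 1+2 against 3+4 for the interview. Power comes from a Fisher exact test on pooled groups "for an alpha of 0.05", and the section adds: "These power calculations are based on the assumption of no interaction effect".

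The Data Analysis section uses a different tool for the same outcome. It states that all analyses will "include an interaction term to account for possible interaction of the 2 main interventions in this study". Under Hypothesis 2a the Acidil comparison is made "using a logistic regression analysis and including an interaction term for the two study interventions". Under Hypothesis 3a the interview comparison is made by "comparing groups 1 + 2 with groups 3 + 4 using a logistic regression analysis and including an interaction term for the two study interventions". The protocol gives no factor coding, no choice between Wald and likelihood-ratio inference, and no fallback for a cell in which nobody or everybody responds.

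**The concern.** Two binary factors and their product need four parameters, and the design has four cells. The model is therefore saturated: each fitted probability equals the observed proportion in its cell. A proportion of 0/6 or 6/6 has an infinite logit, and an average over the cells inherits it. With 6 subjects per cell such proportions are not rare.

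The protocol's stated purpose includes preliminary effect-size estimates for a larger trial. An odds ratio that runs off to infinity, with a Wald interval that means nothing, does not serve that purpose. Hypothesis 2a also makes a further analysis of the continuous score depend on finding no difference between groups, and the protocol does not say how a model without a finite fit counts for that condition. Finally, the power section rests on a simple pooled comparison with no interaction, which is not the model that will be fitted.

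**Working it through.** **Inputs.** Cell size 6, from Overview and Sample Size Justification. Response rates p1 and p2 from the nine rows of Table 2. Placebo response averaging about 19% (range 3–47%) from the Placebo Response background section, and as high as 40% from Possible Benefits. Assumptions: no interview effect, so both Acidil cells share p2 and both placebo cells share p1, and all 24 subjects are evaluable.

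**The plan's own figure.** Table 2 reproduces, all 18 entries within 0.001, from the arcsine approximation to Fisher power, two-sided at 0.05:

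Power = Φ( √(n/2) · 2[asin√(p2 − 1/(2n)) − asin√(p1 + 1/(2n))] − 1.96 ).

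For .25 vs .60 with n = 24 it gives .595, as printed. Here n is the size of each pooled group; the text says "sample sizes of 24 subjects and 20 subjects per group (combining groups 1+3 and 2+4 or groups 1+2 and 3+4 for all analyses". The planned enrolment gives 12 per pooled group. At that size the same formula gives .267, and full enumeration of the two-sided Fisher test gives .292. The gap between 24 and 12 per group is a separate issue; the comparisons below use the enrolment of 12 vs 12.

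**Chance of an empty or full cell.** For one cell, q(p) = p⁶ + (1 − p)⁶. For four cells,

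P(at least one) = 1 − [(1 − q(p1))(1 − q(p2))]².

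Row .25 vs .60: q(.25) = .1782 and q(.60) = .0508, so 1 − (.8218 × .9492)² = 1 − .7800² = .391.

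Under 0/1 reference coding the Acidil coefficient uses only the two cells of one interview type, so the chance is 1 − (1 − q(p1))(1 − q(p2)); in this row, 1 − .7800 = .220.

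**Power.** All 7⁴ = 2,401 possible outcomes were enumerated. The effect-coded Wald statistic is the sum of the two Acidil logits minus the sum of the two placebo logits, divided by the square root of the sum over cells of 1/x + 1/(6 − x). Outcomes without a finite estimate count as no rejection.

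| p1 | p2 | Any cell 0/6 or 6/6 | Reference-coded Acidil term not finite | Wald power, effect coding | Fisher power, 12 vs 12 |
|---|---|---|---|---|---|
| .25 | .50 | .366 | .204 | .091 | .143 |
| .35 | .60 | .233 | .124 | .131 | .146 |
| .45 | .70 | .278 | .150 | .117 | .144 |
| .20 | .50 | .489 | .285 | .094 | .210 |
| .30 | .60 | .300 | .163 | .160 | .211 |
| .25 | .60 | .391 | .220 | .178 | .292 |
| .35 | .70 | .338 | .186 | .202 | .293 |
| .20 | .60 | .510 | .300 | .177 | .392 |
| .30 | .70 | .396 | .223 | .236 | .389 |

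**Sensitivity.** With one common rate p in all four cells, the chance is 1 − (1 − q(p))⁴: .735 at 19%, .188 at 40%, .125 at 47%, and above .99 at 3%. With 5 evaluable subjects per cell it is 36–62% over Table 2's rows.

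**Without the interaction.** A main-effects logistic model on the same four cells was checked for seven of the nine rate pairs (.45/.70 and .35/.70 were not run). It has no finite fit in 1.5–8.9% of trials. For .25 vs .60 the figure is 4.8%, against 39.1% with the interaction.

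**The case against.** **The coding is not stated.** A reader might infer that the planned Acidil coefficient is a 6 vs 6 effect within one interview type, with very little power (about 7% by Wald for .25 vs .60). That holds only under reference coding. The protocol does not specify it, and Hypotheses 2a and 3a name the pooled contrasts. This remains a risk if software defaults are used, not something the plan says. Nor do the two criticisms apply together at full size: the 23–51% belongs to the averaged effect, while the reference-coded term fails in 12–30%.

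**The Wald test is not stated either.** A likelihood-ratio test of the averaged effect is still defined when a cell is empty or full. Its power for .25 vs .60 is about 50%, but its type I error is about 8% when all cells respond at 40%. So the 18% against 29% comparison is specific to Wald inference. A likelihood-ratio p-value still leaves the point estimate infinite.

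**The 73.5% is not the expected case.** It needs all four cells, Acidil included, to respond at 19%. The document does not say that this rate uses the same diary-based responder definition, and it also cites rates up to 40% and 47%.

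**Effect sizes are not all lost.** The outcome is a percentage. Pooled percentages and their difference can be computed whatever the model does, and nothing names the odds ratio as the effect measure.

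**No flat contradiction.** The no-interaction statement concerns the true effects and is disclosed. Examining interaction in the analysis does not contradict it.

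These objections narrow the point. They do not remove it: the protocol itself prescribes the interaction model, so this is more than a detail left to an analysis plan that is not at hand.

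**Conclusion.** The concern holds in a limited form. The model prescribed for 2a and 3a is saturated on four cells of 6. Over Table 2's rates, the chance that the averaged log odds ratio has no finite maximum-likelihood estimate is 23–51%. This assumes no interview effect and full retention. The figure moves with the response rates, as the 19% and 40% cases show, and it rises with dropout. The model also departs from the pooled comparison for which power was calculated. Under Wald inference with effect coding, that departure lowers power from 29% to about 18% at .25 vs .60, and by less in some rows (14.6% to 13.1% at .35 vs .60).

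This should be fixed before analysis, but it is not critical. Feasibility is the primary outcome, the protocol disclaims adequate power, and no decision rule rests on this p-value. The documents do not support the stronger conclusions that the trial will test only a 6 vs 6 effect or will produce no effect-size estimate.

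**What to change.** In Data Analysis, for both 2a and 3a:

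- Take each factor's effect from a main-effects analysis without the interaction. Use either Firth-penalised logistic regression with a profile-likelihood interval, or an exact analysis stratified by the other factor. Plain maximum likelihood is not enough, since the main-effects model can still fail in up to about 9% of trials at the rates checked.
- Report the pooled responder percentages and the risk difference with an exact confidence interval.
- Estimate the interaction in a separate model and report it descriptively with its interval.
- Amend the general statement that every analysis carries the interaction term, so that it agrees.

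The cost is a few sentences and standard software options; no visit, procedure or sample size changes. The small downside is that a main effect averages over any true interaction, which Sample Size Justification already assumes to be absent.

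### Hypothesis 2a produces the continuous last-7-day GERD severity estimate only after a null responder test, and the HRQL ANOVAs in 2c and 3b name no baseline covariate

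*Protocol*

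**What the plan says.** Protocol B3.B, Sample Size Justification, makes feasibility the primary outcome and disclaims efficacy power: "we do not anticipate having adequate power to show significant differences in treatment effects between groups". The stated hope is for effect-size estimates and trends. The main efficacy measure is dichotomous: "Our chief secondary outcome will be the percent of subjects with 50% or greater improvement in heartburn symptom severity".

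Under Data Analysis, Hypothesis 2a, the responder outcome is analysed by logistic regression with an interaction term. The protocol then adds: "If there is no difference between groups, we will perform a secondary analysis using the GERD symptom severity score as a continuous variable". The stated purpose of that step is to look for trends. No model, baseline term or definition of a null result is given. Hypothesis 3a (interview type) is described as analogous, and the fallback is not restated.

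Under Hypothesis 2c: "We will compare GERD-HRQL, Nepean Dyspepsia Index, and SF-12 scores between the Acidil and placebo groups", "incorporating an interaction term for the two main treatment effects, using ANOVA". Hypothesis 3b uses the same wording for the interview factor. Both hypotheses are about greater improvement. The study measures table collects GERD-HRQL, Nepean Dyspepsia Index and SF-12 before the interview at visit 1 and again at visit 2. The text does not say whether the analysed scores are follow-up values or changes.

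Under Hypothesis 2b, GERD and dyspepsia severity over the two weeks is analysed by GEE with a time-by-treatment term for Acidil vs placebo, whatever 2a shows.

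**The concern.** Two choices cost information in a trial of 24 people whose main efficacy product is estimates for planning a larger study.

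First, the continuous endpoint analysis depends on the result of the responder analysis. If the responder test is positive, no continuous last-7-day estimate is planned. If it is null, the same diary data are examined again. Which estimate reaches the planners of the next trial then depends on a test with low power, and the more informative form of the outcome is the fallback. The rule also allows two attempts at 0.05 on one outcome.

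Second, with 6 subjects per cell, chance differences at baseline are likely. An ANOVA of follow-up scores would carry them into the estimated effect, and an ANOVA of change scores uses the baseline less efficiently than ANCOVA does.

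**Working it through.** **Inputs from the protocol.** Design: "We plan to enroll 6 patients into each group for a total of 24 subjects in the study", so each main effect compares 12 with 12. Alpha is 0.05; sidedness is not stated, and two-sided fits Table 2. The responder rates 25% vs 60% are one row of Table 2.

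**Assumed inputs.** The correlation r between baseline and follow-up scores is not in the protocol; 0.3, 0.5 and 0.7 are used. The latent severity score is taken as normal.

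**Table 2 first.** It is stated "for an alpha of 0.05 and sample sizes of 24 subjects and 20 subjects per group". For 25% vs 60% it gives 0.595 (n=24) and 0.497 (n=20). A continuity-corrected normal approximation with 24 or 20 per compared group gives 0.585 and 0.483, and it reproduces all 18 entries within 2 points. Exact Fisher enumeration for this row gives 0.620 and 0.493. The table therefore describes 24 or 20 per compared group. The planned design has 12, so the figures below use 12 vs 12.

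**Cost of the dichotomy, 12 vs 12, 25% vs 60%.**
- Equivalent shift: d = Φ⁻¹(0.60) − Φ⁻¹(0.25) = 0.253 + 0.674 = 0.93 SD.
- Responder test, exact enumeration: Fisher 29%; two-group likelihood ratio 46%.
- Continuous comparison, two-sided t-test, noncentrality 0.928 × √(12/2) = 2.27 on 22 df: 58%.

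The gain from the continuous form is thus 29 points against Fisher and 12 points against the likelihood-ratio test. No power for an adjusted analysis is quoted here. The 0.93 SD comes from responder rates, which are on an improvement scale, and converting it to follow-up-score SDs would need a further assumption.

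**Two attempts at 0.05, no true effect, 12 vs 12.**

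| Responder test | Step 1 alone | Either step |
|---|---|---|
| Fisher | about 1-2% | about 6% |
| Two-group likelihood ratio | about 6-7% | about 8-11% |

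The ranges cover true response rates from 19% to 50%. A Wald test from the planned logistic model with interaction, counting fits that cannot be estimated as non-rejections, gives 5.2% to 7.2% for either step over the same rates. Two independent tests would give 1 − 0.95² = 9.75%.

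**Baseline adjustment.** With follow-up variance σ² and equal variance at baseline, the residual variances are:
- follow-up ANOVA: σ²
- change-score ANOVA: 2(1 − r)σ²
- ANCOVA: (1 − r²)σ²

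| r | ANCOVA / follow-up = 1 − r² | ANCOVA / change = (1 + r)/2 |
|---|---|---|
| 0.3 | 0.91 | 0.65 |
| 0.5 | 0.75 | 0.75 |
| 0.7 | 0.51 | 0.85 |

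The theoretical variance is therefore 9-49% lower than follow-up ANOVA and 15-35% lower than change-score ANOVA. Simulation with 24 subjects, which includes the lost degree of freedom, gives ratios of 0.96, 0.79 and 0.54 against follow-up and 0.68, 0.79 and 0.89 against change: savings of 4-46% and 11-32%.

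**Chance imbalance.** P(|baseline difference| > 0.5 SD) = 2Φ(−0.5/√(2/n)), which is 22% for n = 12 per side and 39% for two cells of 6.

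**The case against.** Several stronger readings are tempting, and the protocol does not support them.

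- *GERD severity is never analysed continuously unless 2a is null.* This is not so. The 2b GEE is unconditional, as are the counts of heartburn-free days under 2b and the exploratory GSRS comparison, which includes a reflux subscale. This objection stands against any general claim. It does not remove the narrower point: the GEE targets trajectory and covers only Acidil vs placebo, and the GSRS is a different instrument. None of these gives the last-7-day diary effect for each factor.
- *The HRQL analysis ignores baseline.* That is an inference. ANOVA of change scores would fit the hypotheses and is not excluded, and the choice could be settled in an analysis plan that is not at hand. What stands is that the protocol names ANOVA and no baseline covariate, and ANCOVA has lower theoretical variance on either reading.
- *The two-step rule seriously inflates false positives.* The excess is modest. The second step is labelled secondary and for trends, and the pilot makes no confirmatory efficacy claim. The argument does not reach HRQL, and it reaches 3a only by analogy.
- *The dichotomy halves power and also pushes error to 8% or more.* That pairs Fisher for power with the likelihood-ratio test for error. With one test throughout, the figures are 29% vs 58% power with about 6% error (Fisher), or 46% vs 58% with about 8-11% (likelihood ratio).

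The protocol's remark that the sample is too small to adjust concerns confounders in the 3c logistic model. It does not speak against one prespecified baseline covariate in a linear model.

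**Conclusion.** The point holds as a low-cost improvement to the plan. It does not invalidate the trial. The continuous last-7-day severity estimate should not depend on a null responder test, because the pilot exists partly to estimate effects. In the 25% vs 60% example the continuous comparison has 58% power against 29% or 46% for the dichotomy, under a normal model. For HRQL, ANCOVA lowers the theoretical variance by 9-49% against follow-up ANOVA or 15-35% against change-score ANOVA, for assumed r of 0.3 to 0.7; the protocol supplies neither r nor an SD. The chance of a false positive at either step, about 6% with Fisher and about 8-11% with a two-group likelihood-ratio test, is a secondary consideration.

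**What to change.** 1. In Hypothesis 2a, delete the opening condition of the sentence on the continuous analysis. State that last-7-day GERD severity will always be estimated by ANCOVA on the baseline-week score, with both factors and their planned interaction, and report the estimate and 95% CI for each factor. This also settles what is planned for 3a.
2. In Hypotheses 2c and 3b, replace ANOVA with ANCOVA of the 2-week GERD-HRQL, Nepean and SF-12 scores on the corresponding baseline score, both factors and the interaction.
3. Keep the responder analysis and the 2b GEE as they are.

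The cost is wording and one residual degree of freedom per model (24 − 4 = 20 becomes 19). The baseline diary and questionnaires are already collected, so no visit or measurement changes.
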